**
[figure not shown]
**

###### UNDP/World Bank/WHO Special Programme for Research & Training in Tropical Diseases (TDR)

TITLE: **A TWO-ARM SINGLE-BLIND RANDOMISED COMPARISON OF FOUR FIXED -DOSE COMBINATIONS VERSUS STANDARD TREATMENT WITH SEPARATE ANTI-TB DRUGS FOR TREATMENT OF PULMONARY TUBERCULOSIS**

PRODUCTS: Test arm: 4 FDC formulation (Ethambutol (275 mg)/ Rifampicin (150 mg)/ Isoniazid (75 mg)/ Pyrazinamide (400 mg) followed by 2 FDC formulation (Rifampicin (150 mg)/ Isoniazid (75 mg))

Control arm: Loose formulations of Ethambutol (400 mg), Rifampicin (450 mg), Isoniazid (225 mg), Pyrazinamide (400 mg) followed by loose formulations of Rifampicin (150 mg), Isoniazid (225 mg) and Isoniazid (100 mg)

Version: Final (July 2008)

Design: Single-blind, randomised controlled trial

Study site: Multi-centre (Ethiopia, Nigeria)

Principal Investigator: [name] (Ethiopia)

[name] (Nigeria)

Study Statistician: [name]

Study Director: [name] IRM/TDR/WHO

Project Manager: [name] (WHO)

TABLE OF CONTENTS

A TWO-ARM SINGLE-BLIND RANDOMISED COMPARISON OF FOUR FIXED-DOSE COMBINATIONS VERSUS STANDARD TREATMENT WITH SEPARATE ANTI-TB DRUGS FOR TREATMENT OF PULMONARY TUBERCULOSIS [1](#__RefHeading___Toc130201393)

2. RATIONALE AND OBJECTIVES [2](#__RefHeading___Toc130201394)

7.7 Protocol Amendments [13](#__RefHeading___Toc130201424)

# A TWO-ARM SINGLE-BLIND RANDOMISED COMPARISON OF FOUR FIXED-DOSE COMBINATIONS VERSUS STANDARD TREATMENT WITH SEPARATE ANTI-TB DRUGS FOR TREATMENT OF PULMONARY TUBERCULOSIS

1. BACKGROUND INFORMATION

Tuberculosis (TB) continues to be a major global public health problem **1-5**. Approximately two billion people worldwide are infected with *Mycobacterium tuberculosis* (MTb). The global incidence of active tuberculosis (TB) is estimated at 8.8 million new cases per year—25,000 new cases each day **2**. In developing countries—home to 95% of TB cases and 98% of TB deaths—tuberculosis causes 25% of the burden of preventable diseases. In 1991, the World Health Assembly adopted targets of detecting 70% of all infectious TB cases and curing at least 85% of detected cases by 2005.2 Despite intensified efforts, these unexceptional targets have not yet been met.3 At the end of 2005, 82% of TB cases were successfully treated, but only 45% of infectious TB cases were detected.4 Detection and cure rates are especially low in sub-Saharan Africa and other high HIV prevalence settings.5

Combined preparations of antituberculosis drugs have been widely used. The use of fixed-dose combined (FDC) drugs in the treatment of tuberculosis by National Tuberculosis Programmes (NTPs) has been recommended by the World Health Organisation (WHO) and the International Union Against Tuberculosis and Lung Disease (IUATLD).6 There may be many advantages of FDC drugs; they could aid compliance and hence increase cure rates, could include preventing the emergence of drug resistance due to monotherapy, reduce the risk of incorrect dosage and simplify procurement and prescribing practices.

The recommended treatments for newly diagnosed tuberculosis always contain an initial intensive phase of four drugs. The most widely used four-drug regimen consists of rifampicin, isoniazid, pyrazinamide and ethambutol. Two and three-drug FDCs, containing isoniazid and rifampicin, have been in use for a number of years. Several pharmaceutical companies have manufactured a combined fixed dose tablet containing these four drugs. Their bioavailability levels have been evaluated as acceptable when compared to those given in separate drug formulations.7,8 It has been reported that the combined tablets are well tolerated and the rate of side effects similar to that of the separate formulations. 9, 10

# 2. RATIONALE AND OBJECTIVES

# 2.1 Rationale

Owing to the length (6-8 months) and complexity (4 drugs, up to 16 tablets a day) of the current treatment, the delivery of short-course chemotherapy for TB with single drug formulations is challenging and poses risks of prescription errors and lack of compliance with treatment where DOTS is either poorly or not used. Drug supply management is complicated, since individual drugs must frequently be ordered from different sources, and there is a risk of out-of-stock situations, in which patients may be treated with too few drugs, or even only one drug in isolation. Another major concern in the treatment of tuberculosis is to prevent the emergence of drug resistance especially to isoniazid and rifampicin, the two most potent antitubercular drugs.

One approach to tackling these challenges is to use fixed dose combinations (FDCs) of the four and two TB drugs that are used in the intensive and maintenance phases, respectively. However, these drugs have been little used to date despite being recommended by the WHO and the IUATLD. One concern is the variable bioavailability of rifampicin in poor quality fixed dose combinations. Some rifampicin containing FDCs with adequate absorption in healthy normal volunteers have been endorsed by the WHO.6Poor absorption may occur in HIV infected individuals.

The advantages of FDCs over loose drugs could include the following:

- The emergence of HIV/AIDS has complicated treatment of TB among co- infected patients (HIV-infected TB cases). The increasing availability of HAART (highly active antiretroviral therapy) in the public sector in resource-limited settings and the increasing mortality among HIV-infected TB cases managed alone with TB drugs implies the need for concomitant treatment of HIV and TB. 4FDCs presents a rational approach to managing the huge burden that would otherwise ensue in these categories of patients, which could lead to drug resistance from dropping off some TB medications in loose formulations.
- It is expected that 4 FDCs limit the risk of emergence of drug resistant tuberculosis by using a simplified treatment regimen and increasing treatment compliance which may reduce the probability of monotherapy11. In a study conducted in Hong Kong comparing 3FDCs (Isoniazid, Rifampicin, Pyrazinamid) with loose anti TB treatment, it is reported that only 1% of 312 patients who received 3FDCs complained about difficulty of swallowing or the quantity of drugs to be ingested compared with 5% of 308 patients receiving the loose preparations. Although it is expected that 4FDCs may therefore improve the patient's compliance with treatment, to date no double blind randomized trials have been conducted to evaluate the patient's compliance with 4FDCs12 .
- With single drug formulations, there are at least three reasons which contribute to the drug non-availability: inadequate stock, delay in receipt of orders and no replacements available on reaching the expiry date. The above issues could also exist with the 4FDCs treatment, however because of fewer drug formulation orders, shipments and distribution involved, the efficacy of drug supply system could be well improved11.
- As rifampicin is also used for treatment of some other common infectious diseases such as atypical pneumonia and sexually transmitted diseases, black-market sales of this drug are not uncommon in countries where other antibiotics are unavailable11. Therefore, use of rifampicin as a broad spectrum antibiotic for conditions other than tuberculosis could lead to its usage as mono-therapy to patients who may also suffer from tuberculosis. Treating a tuberculosis patient with mono-therapy of rifampicin rapidly leads to resistance even if it is given for a short period only. In combination drugs, the presence of isoniazid could reduce the probability for the survival of rifampicin-resistant mutants.
- Due to the enormous costs involved in treating drug-resistant tuberculosis, preventing the emergence of drug resistance must be given the highest priority. Mitchison argues that multiple interruptions of treatment regimes are considered the predominant cause of drug resistance TB13. When using single-drug formulations, due to the length (6-8 months) and complexity (four drugs, up to 16 tablets per day) of the treatment patients are more prone to continue their treatment with one drug while interrupting the others, thus it creates a risk of mono-therapy and selection of drug resistant mutants. Hence a clinical trial should be conducted to address such issues.
- In the past, some researchers claimed that adverse reactions to 3FDCs are not more common than loose combination anti-TB. To date, no data is available on the safety and adverse reactions associated with 4FDCs.

In conclusion, if their potential is realized, the 4FDCs and 2FDCs can be a means of improving TB control but FDCs have not been assessed adequately in countries like Ethiopia and Nigeria where HIV seropositivity among TB patients is high. Therefore, there is a need to increase the evidence base on which to recommend FDCs in TB control programme and other settings.

## 2. 2 General Objectives

To measure the efficacy and assess safety of fixed dose combination therapy (FDCs) compared to separate loose formulation therapy in pulmonary tuberculosis.

###

### ***Primary Outcome measures***

- cure rates at end of treatment (6 months). A cure is defined as one negative sputum culture in patients who did not fail treatment. A treatment failure is defined as:

1. a patient who is persistently smear positive by five months of treatment
2. a patient who becomes smear negative but positive again at or after five months of treatment (note: sputum positivity before this time is not considered a treatment failure)

- ***Secondary outcome measures***
- early response rates: proportion of patients with negative culture results at 8 weeks after initiation of therapy
- proportion of patients with relapses during the 72 weeks follow up period after the end of treatment. A relapse is a patient previously treated for tuberculosis who has met the case definition of cure (as defined above) and been declared cured by a physician and who has now been diagnosed with bacteriologically positive (two positive smears and culture positive) tuberculosis. If there is discordance between smear and culture results, a clinical decision will be made regarding further management: (i) smear positive, culture negative, and (ii) smear negative and culture positive.
- cure rates in HIV positive TB patients
- proportion of patients with clinical deterioration of pulmonary tuberculosis with the need for hospitalisation
- proportion of patients with *serious* adverse events any time during chemotherapy
- proportion of patients with any adverse events during chemotherapy
- proportion of patients completing treatment (defined as patients who achieved a total of 54 out of 56 doses in the first eight weeks of treatment AND 107 out of 112 doses at a daily rate during the subsequent 16 weeks of treatment) within each group. (96% doses taken considered as completed in intensive and maintenance phases).
- Proportion of patients who developed MDR-TB

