***Study withdrawals***

- AFB smear positive patients found later to be culture negative. These patients will be withdrawn from the study but they will be assessed clinically to see if treatment should be continued or not. (This occurs in 1-5 % of newly diagnosed cases).
- Patients withdrawing consent in the course of the trial
- Antiretroviral therapy initiation within the first six months of anti-TB medication.
- AFB smear positive patients at week 20 whose sputum culture and DST confirm resistant to isoniazid and rifampicin (MDR TB)
- Drug toxicity necessitating interruption of treatment

Patients who withdraw from study or are lost to follow up will however still be included in the intention to treat (ITT) analyses set.

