**Week 36 Week 48 Week72 Week 96**

(End of trial)

| Study procedures | Screening | Enrolment  Study Drug  T=0h | Week 8  (end of intensive phase) | Week  20 | Week 24  (end of continuation phase) | (Weeks 36,48,72 and 96) |
| --- | --- | --- | --- | --- | --- | --- |
| Medical History | X |  |  |  |  |  |
| Physical Examination | X |  | X | X | X | X |
| Sputum for AFB smear | X |  | X | X | X | X |
| Sputum for culture |  | X | X | Xa | X | Xa |
| Sensitivity testing |  |  |  | Xb |  |  |
| Informed consent | X |  |  |  |  |  |
| Haematology and Clinical chemistry | X | X | X | X | X | X |
| Urine analysis | X | X |  |  |  |  |
| Pregnancy test | X |  |  |  |  |  |
| HIV testing  CD4 test | X  Xd |  |  |  | Xd | Xd |
| Randomisation |  | X |  |  |  |  |
| Drug administration |  | X | X | X | Xe |  |
| Adverse Events |  | Symptom checklist | X | X | X | X |

Xa It the sputum smear is positive

Xb Sensitivity testing of screening smear and 5 month smear if sputum is positive.

Xd CD4 testing only for HIV positive TB patients. Repeat CD4 test on weeks 24, 48, 72 and 96. Not indicated at week 36.

Xe By the end of week 24, treatment should be completed.

Patients will be instructed to attend the TB treatment centre, for the duration of treatment; both the intensive and maintenance phases. All drug doses will be administered under observation and documented by the trial nurse. All drug doses in the continuation phase will be administered under standard operation of DOTS of the country. Patients will also be evaluated for clinical, haematological and biochemical parameters during these follow up period.

Trial subjects will be followed up for 72 weeks after the completion of treatment. They will be required to come to TB treatment centre for clinical, haematological and biochemical assessments at the end of 36 weeks ,48 weeks ,72 weeks and 96 weeks after initiation of treatment. A home visitor will trace individuals who fail to come at the specified time points. At each follow-up time, subjects will provide three sputum samples: one spot, one morning and a second spot sputum specimens for smear examination at each of the three follow up visits. Cultures will be done only for smear positive individuals (as defined above).

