# 5. ASSESSMENT OF SAFETY & TOLERABILITY

**5.1 ADVERSE EVENTS**

Safety will be assessed by monitoring the occurrence of adverse events. An adverse event is a symptom, sign, clinical illness, or an abnormal laboratory result that was either: (i) not present on Day 0 but occurred during follow-up, or (ii) was present on Day 0 but has since become worse. There will be a checklist of symptoms and signs that will be sought at each assessment (see CRF). Routine laboratory tests (detailed in the CRF) will be done at baseline and repeated only as clinically indicated during follow-up. Other laboratory tests will done if clinically indicated.

**All adverse events will be graded as: 0=normal, 1=mild, 2=moderate, 3=severe** according to ICH Clinical Safety Data Reporting. An assessment of the cause of the adverse event will be done by the clinicians. The relationship to study drug will be graded as (i) none, (ii) unlikely, (iii) possible, (iv) probable, (v) definite, (vi) unknown. Refer to the WHO/TDR SOP for these definitions. Adverse events will be treated on their merits and patients followed up as necessary. All adverse events will be recorded in the CRF. All serious and unexpected adverse events, as defined in the SOPs, will be recorded in the SAE form (see below). Necessary details will include: (i) the description of adverse event, (ii) onset date, (iii) speed of inset: sudden, gradual, unknown, (iii) duration, (iv) severity, (v) relationship to study drugs, (vi) outcome, (vii) measures taken (symptomatic treatment, discontinuation of treatment).

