## 6.4 Data analysis

The database file generated thus will be converted into statistical package STATA software version 7 (STATA Corporation, Texas, USA) and analysed by the study statistician, and PI in collaboration with the study director. Analysis will be both (a) by intention-to-treat, and (b) per protocol (excluding those who did not receive adequate chemotherapy or were withdrawn from the study), including survival analysis.Subjects will be compared based on their assigned treatment using chi-square, Student's t-test or the Wilcoxon rank sum test as appropriate depending on the scale of measurement and the validity of underlying assumptions for the baseline characteristics. Primary and secondary outcomes for each study subject will be recorded as positive (desirable) and negative (not desirable) at a pre-specified time. For primary outcome Chi-square will be used to compare proportions of culture positive and culture negative subjects at the end of the study in the two treatment groups. The effects of confounding variables (such as age and sex) will be adjusted using multiple logistic regression. In model construction, backward elimination will be employed using important independent variables initially. An alpha of 0.10 will set the significance level for entering a variable into the model. Chi-square will also be used to compare differences in each of the three secondary end points. In the whole analysis, an alpha of 0.05 will set the significance level for testing the null hypothesis. In presenting results exact p-value as obtained from the computer program will be presented.

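### Both safety outcomes stop counting when chemotherapy stops, and toxicity that interrupts treatment withdraws the patient, so a reaction that turns serious afterwards is, read literally, left out of the SAE outcome

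*Protocol*

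**What the plan says.** Only the protocol is at hand.

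- **Outcome window (section 2.2, secondary outcomes).** The SAE outcome is the proportion of patients with serious "adverse events any time during chemotherapy". The companion outcome is the "proportion of patients with any adverse events during chemotherapy". No post-dose period is given for either.
- **Withdrawal (section 3.2, Study withdrawals).** One listed reason is "Drug toxicity necessitating interruption of treatment", with no threshold for severity or duration.
- **Analysis sets.** Section 3.2 states: "Patients who withdraw from study or are lost to follow up will however still be included in the intention to treat (ITT) analyses set". The per-protocol analysis in section 6.4 is described as "excluding those who did not receive adequate chemotherapy or were withdrawn from the study".
- **Schedule (section 3.6).** The table footnote reads "Xe By the end of week 24, treatment should be completed". The text adds: "Trial subjects will be followed up for 72 weeks after the completion of treatment". The adverse event row is also marked at weeks 36, 48, 72 and 96.
- **AE and SAE handling (sections 5.1 and 5.2).** An AE includes a finding "not present on Day 0 but occurred during follow-up", which does not depend on being on drug. Duration, severity and outcome are recorded. Patients with an AE are followed as needed, with no schedule or end date. All SAEs must be reported within 24 hours, with no restriction to the treatment period.

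**The concern.** The reaction that the outcome is meant to measure can close its own counting window. When toxicity leads to the drugs being stopped, chemotherapy ends for that patient, the outcome stops counting, and the patient is recorded as withdrawn. Anything serious that follows then has no clear place in the SAE outcome.

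Safety is half of the general objective in section 2.2, and section 2.1 says that safety data on the four-drug combination are lacking. If one arm has more toxicity stops, its patients have less counted time, and the SAE comparison can lean in that arm's favour.

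**Working it through.** The protocol gives no safety rate, so there is no stated figure to reproduce. The check sets the outcome window against the withdrawal rule and asks which events are counted.

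**1. Is the window stated or left open?** It is stated. The same outcome list gives relapse its own window in the 72 weeks after treatment. The protocol therefore separates treatment time from follow-up time and places both safety outcomes in the first.

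**2. Which events are counted?** The timings below are illustrative. For a stop at week 4, the literal window closes 24 − 4 = 20 weeks before the planned end of treatment.

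| Case | Any-AE outcome, literal reading | SAE outcome, literal reading | SAE outcome if chemotherapy means the planned 24 weeks |
| --- | --- | --- | --- |
| A. Already serious while on drug, then stopped | counted | counted | counted |
| B. Not serious at stop in week 4, serious in week 6 | counted | not counted | counted |
| C. New reaction in week 5 after a stop in week 4, serious | that reaction not counted | not counted | counted |
| D. Starts days after the last dose at week 24, serious | not counted | not counted | not counted |

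If an event is attributed by its onset and its later outcome is carried back, case B is counted as well. Cases C and D are not.

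**3. Does another section close the gap?**

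- The intention-to-treat rule keeps the patient in the denominator. It does not move a post-stop event into the numerator.
- The later AE visits and the SAE reporting rule mean that such events may well be recorded. The outcome as worded still does not count them.
- Follow-up is anchored on completing treatment, and the visits are counted from its start. Neither sentence says whether a patient withdrawn for toxicity attends them.
- The per-protocol set leaves these patients out altogether.

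**4. Effect on the comparison.** For arm *i*, let *p* be the true risk of an SAE over a fixed period, *s* the risk of a toxicity stop, and *q* the chance that a stopped patient's first serious event comes after the stop. The counted risk is *p_i* − *s_i q_i*. The counted difference between arms is then

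(*p_1* − *p_2*) − (*s_1 q_1* − *s_2 q_2*).

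With the same *q* in both arms the shift is −*q*(*s_1* − *s_2*). It is zero when toxicity stops are equally frequent, and it favours the arm with more stops otherwise. The protocol gives no value for *p*, *s* or *q*, so neither the number of patients lost nor the shift can be calculated.

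**The case against.** The other side has four good arguments.

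- **The SAE definition is broad.** Section 5.2 includes events that need acute treatment. Many reactions bad enough to interrupt therapy would already qualify on drug and be counted (case A). This stands. A reader might infer that the serious consequences of toxicity are lost in general, but the protocol does not support that. Only later escalation or onset after stopping is at risk.
- **Collection is wider than the outcome.** AE assessment runs to week 96, home visitors trace patients who miss visits, outcomes are recorded and all SAEs are reported. This also stands. It would be wrong to infer that the protocol stops recording events once drugs stop. What is missing is an express statement that patients withdrawn for toxicity stay on those visits.
- **Chemotherapy is undefined, and an interruption need not be permanent.** If the word means the planned 24 weeks, cases B and C are inside the window and only case D is left. That reading is possible, but the protocol does not state it.
- **The analysis plan can settle this.** Section 6.5 defers the plan, and the length of a post-dose period is often set there. That is fair as to length. But the protocol has fixed the window in the outcome itself, so a plan that counted events after the last dose would depart from the literal text.

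A reader might also infer a material loss of SAEs or an actual bias between arms. Neither is shown. The arms receive the same drugs at similar nominal doses. At 40-54 kg rifampicin, isoniazid and pyrazinamide match (450, 225 and 1200 mg), and ethambutol is 3 × 275 = 825 mg against 2 × 400 = 800 mg. At 55-70 kg the same three match (600, 300 and 1600 mg), and ethambutol is 4 × 275 = 1100 mg against 3 × 400 = 1200 mg. Nothing in the protocol indicates that toxicity stops will differ by arm.

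**Conclusion.** The point holds in a limited form. As worded, the SAE outcome can miss a reaction that becomes serious only after the drugs are stopped, or that begins soon after the last dose. The any-AE outcome is affected less, because the reaction that triggers the stop is itself counted.

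This rests on reading chemotherapy as time actually on study drug. On the planned-24-weeks reading, only events starting after week 24 are lost. The size cannot be calculated from the protocol. If toxicity stops are balanced, both arms' rates are understated and the difference is not shifted; bias requires the stops to differ by arm. The primary cure outcome is not touched. This is a cheap improvement to a secondary safety outcome.

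**What to change.** Amend the two safety outcomes and the withdrawal text:

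1. Define both outcomes from first dose to a fixed end point that does not depend on withdrawal, for every patient who took a dose. One option is the later of week 24 or a set number of days after the last dose. The sponsor should choose and justify that number.
2. Attribute an event by its onset, and count it as serious if it later becomes serious.
3. State in section 3.2 that withdrawal for toxicity does not end AE and SAE collection, and that these patients remain on the scheduled safety assessments. This concerns data collection only and changes no treatment rule.
4. Report the on-chemotherapy count as a supportive analysis.

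The cost is a wording amendment with ethics review. It uses visits and home tracing already in section 3.6. The downside is that some events arising on later non-study treatment will be counted, and SAE rates will look slightly less favourable. The supportive count lets a reader see how much that matters.
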